# Doxapram versus placebo in preterm newborns: a study protocol for an international double blinded multicentre randomized controlled trial (DOXA-trial)

**DOI:** 10.1186/s13063-023-07683-5

**Published:** 2023-10-10

**Keywords:** Doxapram, Placebo, Randomized controlled trial, Preterm infants, Apnoea of prematurity, Efficacy and safety

## Abstract

**Background:**

Apnoea of prematurity (AOP) is one of the most common diagnoses among preterm infants. AOP often leads to hypoxemia and bradycardia which are associated with an increased risk of death or disability. In addition to caffeine therapy and non-invasive respiratory support, doxapram might be used to reduce hypoxemic episodes and the need for invasive mechanical ventilation in preterm infants, thereby possibly improving their long-term outcome. However, high-quality trials on doxapram are lacking. The DOXA-trial therefore aims to investigate the safety and efficacy of doxapram compared to placebo in reducing the composite outcome of death or severe disability at 18 to 24 months corrected age.

**Methods:**

The DOXA-trial is a double blinded, multicentre, randomized, placebo-controlled trial conducted in the Netherlands, Belgium and Canada. A total of 396 preterm infants with a gestational age below 29 weeks, suffering from AOP unresponsive to non-invasive respiratory support and caffeine will be randomized to receive doxapram therapy or placebo. The primary outcome is death or severe disability, defined as cognitive delay, cerebral palsy, severe hearing loss, or bilateral blindness, at 18–24 months corrected age. Secondary outcomes are short-term neonatal morbidity, including duration of mechanical ventilation, bronchopulmonary dysplasia and necrotising enterocolitis, hospital mortality, adverse effects, pharmacokinetics and cost-effectiveness. Analysis will be on an intention-to-treat principle.

**Discussion:**

Doxapram has the potential to improve neonatal outcomes by improving respiration, but the safety concerns need to be weighed against the potential risks of invasive mechanical ventilation. It is unknown if the use of doxapram improves the long-term outcome. This forms the clinical equipoise of the current trial. This international, multicentre trial will provide the needed high-quality evidence on the efficacy and safety of doxapram in the treatment of AOP in preterm infants.

**Trial registration:**

ClinicalTrials.gov NCT04430790 and EUDRACT 2019-003666-41. Prospectively registered on respectively June and January 2020.

**Supplementary Information:**

The online version contains supplementary material available at 10.1186/s13063-023-07683-5.

## Background

Apnoea of prematurity (AOP), a cessation of breathing, is one of the most common symptoms of an immature breathing system and affects almost 80% of the preterm infants born below a gestational age (GA) of 28 weeks [1]. This poor respiratory control leads to episodes of intermittent hypoxemia and bradycardia. Hypoxemic episodes, especially if prolonged, are associated with increased risks for late death or disability, including motor impairment, cognitive or language delay and risk for visual impairment [2, 3].

Non-invasive respiratory support and caffeine therapy are typically administered to prevent intermittent hypoxemia in preterm infants [4]. Endotracheal intubation and invasive mechanical ventilation can resolve persisting AOP by decreasing the frequency and intensity of hypoxemic episodes, but are associated with an increased risk for bronchopulmonary dysplasia (BPD) and neurodevelopmental impairment [5, 6]. The use of invasive mechanical ventilation is therefore restricted as much as possible in preterm infants. Until now, no consensus has been reached on the optimal treatment strategy for AOP because high-quality trials are lacking.

Doxapram, a respiratory stimulatory analeptic drug, might be considered as an add-on treatment to non-invasive respiratory support and caffeine treatment for persisting AOP in preterm infants. It stimulates the respiratory drive through the brainstem respiratory centre, and the peripheral carotid and aortic chemoreceptors [7]. Unfortunately, well-designed and adequately powered trials on the clinical effect of doxapram are missing. Several observational studies found that treatment with doxapram can be beneficial in reducing the apnoea rate and the number of hypoxemic episodes [8–10]. Doxapram therapy may also be effective in preventing preterm infants from invasive mechanical ventilation [11]. Doxapram may potentially improve neonatal outcomes by preventing preterm infants from the risks, including development of BPD, associated with hypoxemic episodes and invasive ventilation.

On the opposite, concerns on the safety of doxapram are also reported in literature. Described adverse effects include hypertension, irritability, tachycardia, hypokalaemia, gastro-intestinal problems and a prolonged QT interval [12–17]. Some observational studies recommended restricted use of doxapram in preterm infants as they found increased cerebral oxygen consumption, decreased cerebral blood flow, increased electrographic seizure activity (based on amplitude-integrated electroencephalography, aEEG) and less sleep-wake cycling during treatment [18, 19]. The limited studies describing the long-term effects of doxapram are inconclusive. In a cohort study, ten Hove et al. did find a lower risk of the combined outcome death or neurodevelopmental delay in preterm infants treated with doxapram compared to controls that did not receive doxapram after adjusting for confounding factors (OR = 0.54, 95% CI 0.37, 0.78) [20]. On the contrary, Lando et al. [21] found that doxapram treatment may have a negative effect on neurodevelopmental outcome. Although doxapram might reduce AOP and seems effective to avoid invasive ventilation on the short term, its long-term effects are to be revealed.

To our knowledge, no adequately powered, well-designed, randomized placebo-controlled trial has been performed to study the long-term efficacy and safety of doxapram in the clinical setting [10]. In this study, we hypothesize that doxapram is safe and effective in reducing the composite outcome of death or severe disability at 18 to 24 months corrected age as compared to placebo.

## Methods and analysis

### Trial design

The DOXA-Trial is a multicentre, double blinded, randomized, placebo-controlled trial with two arms, designed to evaluate the superiority of doxapram compared with placebo in the treatment of AOP. This study protocol followed the SPIRIT (Standard Protocol Items: Recommendations for Interventional Trials) guidelines [22], whereas the trial will adhere to the CONSORT (Consolidated Standards of Reporting Trials) statement [23].

### Study setting

Patients will be recruited from neonatal intensive care units (NICUs) of the participating centres in the Netherlands, Belgium and Canada. Recruitment started in August 2020 and is expected to continue for 4 years. The DOXA-trial is coordinated by the Neonatology Network Netherlands (N3) for the Dutch centres, the University Hospitals Leuven for the Belgian centres and the Maternal Infant Child and Youth Research Network MICYRN for the Canadian centres. Participation of additional (international) centres during the trial is encouraged.

### Study participants

Patients are eligible for inclusion if the following criteria are met: (1) GA at birth below 29 weeks, (2) postnatal age of at least 120 h, (3) adequately dosed caffeine (max 50% increase above standard daily maintenance dose), (4) non-invasive respiratory support according to the local treatment policy, (5) frequent and/or severe apnoea that require a medical intervention as judged by the attending physician (indication to start doxapram, to provide additional caffeine or to start mechanical ventilation if not included in the trial) and (6) written informed consent of parents or legal representatives. A pragmatic study design is chosen, because we anticipate considerable variation between centres and physicians in the judgment on what frequency and duration of apnoea is considered unacceptable and requires intervention.

Exclusion criteria are as follows: (1) previous use of open label doxapram, (2) use of theophylline to replace doxapram, (3) chromosomal defects, (4) major congenital malformations that compromise lung function resulting in chronic ventilation, or increase the risk of death or adverse neurodevelopmental outcome and (5) palliative care or treatment limitations because of high risk of impaired outcome.

Several conditions, such as sepsis, pneumonia, necrotizing enterocolitis (NEC) and patent ductus arteriosus may present with apnoea and respiratory failure. Distinction from apnoea caused by prematurity is difficult or even impossible. Therefore, the suspicion of one of these diagnoses is not considered an exclusion criterion. However, the diagnosis may result in a decision to primarily intubate the infant and not include the patient in the trial at that time point. This decision is left to the attending physician and medical team. Discontinuing study medication is always allowed if judged necessary by the attending physician and medical team, although discouraged to prevent more open label treatment in the placebo group.

### Pharmacological intervention

Participants will be randomized to receive either doxapram (as hydrochloride, 2 mg/ml in dextrose 5%, 50 mL) or placebo (dextrose 5%, 50 mL). Study medication is manufactured in ready to use 50-mL polypropylene vials and labelled by *Apotheek A15* in Gorinchem, the Netherlands, according to Good Clinical Practice and Good Manufacturing Practice guidelines. Doxapram and placebo fluids are visually identical as well as the labels and the vials, and the syringes in which the study medication will be prepared for blinded administration. Central stock of study medication is stored in the trial pharmacy of Erasmus MC in Rotterdam and dispensed to participating hospitals to supply the local stock.

Therapy is started with a loading dose of 2.0 to 2.5 mg/kg administered intravenously in 10 min, followed by a continuous maintenance dose of 0.5 to 1.0 mg/kg/h via intravenous infusion [17, 24]. The maintenance dosage can be titrated based on the clinical response of the patient; an increase of 0.5 mg/kg/h is recommended after 30–60 min in case of an insufficient effect of the study medication. Increases are allowed up to 2.0 mg/kg/h. If the study medication is effective, clinicians are encouraged to assess the possibility of step-by-step dose reduction of 0.5 mg/kg/h every 12–24 h. Dosage adjustments can also be made if side effects are suspected. Using the same formulation, a switch to gastro-intestinal administration via the nasogastric tube is feasible and allowed [25]. Gastro-enteral administration can be either continuous or intermittently from 4 times daily up to 24 times per day. Oral administration of the study medication requires a 33% higher dose, with a maximum dose of 2.0 mg/kg/h, compared to intravenous administration, due to the oral bioavailability of doxapram (74%) in preterm neonates [26].

Therapy is continued until the number and duration of the apnoea decrease below the estimated intervention threshold, or until respiratory failure occurs and invasive mechanical ventilation is needed according to the discretion of the attending physician (Figs. 1 and 2). Physicians are allowed to shortly interrupt the continuous administration of study medication in order to administer other (incompatible) medication intravenously. If the study medication is paused for less than 2 h, no additional action is necessary. An additional half-loading dose of the study medication should be administered if the interruption lasts between 2 and 4 h and a standard loading dose if the pause lasts longer than 4 h.

**Fig. 1 Fig1:**
[figure not shown]
Overview of the study procedures

**Fig. 2 Fig2:**
[figure not shown]
Schedule of enrolment, interventions and assessments

In case of recurrent apnoea needing intervention after down-titration and study medication cessation, the study medication can be restarted according to the same guidelines as the first administration. Open label use of doxapram in participants of this study is prohibited. A patient will remain in the same randomized study group.

#### Primary outcome

The primary outcome is the composite outcome of death or severe disability at 18 to 24 months corrected age.

Severe disability will be defined as having one or more of the following outcomes at the age of 18 to 24 months: cognitive delay, cerebral palsy, severe hearing loss, or bilateral blindness. Cognitive delay will be defined as a Mental Development Index score of less than 85 on the Bayley Scales of Infant and Toddler Development III [27]. Cerebral palsy will be diagnosed if the patient had a non-progressive motor impairment, characterized by abnormal muscle tone and decreased range or control of movements. The level of gross motor function will be determined with the Gross Motor Function Classification System and is defined as severe movement disability if the score is > level 2 [28].

Severe hearing loss will be defined as hearing loss requiring hearing aids and will be measured by audiometry in patients with signs of hearing abnormalities at the corrected age of 18 to 24 months [29]. Hearing will be assumed to be normal in participants with a normal hearing screening after birth and no signs of hearing abnormalities at the corrected age of 18 to 24 months. Severe visual impairment or blindness will be defined as a corrected visual acuity less than 20/200 [30].

#### Secondary outcomes

Secondary outcomes with details on the statistical analyses are summarized in Table 1.

**Table 1 Tab1:** Summary of the secondary objectives with the statistical analysis and time of measurement

	**Secondary outcomes**	**Details of statistical analysis**^**a**^	**Time of measurement**
**Short-term mortality and comorbidity**	- Bronchopulmonary dysplasia (NICHD criteria) - Death	Logistic regressions will be performed, corrected for GA and centre, for BPD and death separately, and the combined outcome of BPD and death. Survival analysis will be performed for time to death. Cause-specific risk models will be computed to consider death as competing risk for severe disabilities at 18 to 24 months of age.	Postmenstrual age of 36 weeks and hospital discharge
	**Admission:** - Length of stay intensive care - Length of stay hospital	Survival analyses will be performed for time to discharge.	Hospital discharge
	**Respiration:** - Incidence of endotracheal intubations - Number of days on invasive ventilation - Number of days on respiratory support - Number of days with supplemental oxygen - Respiratory complications - Use of postnatal corticosteroids	Logistic regression analysis will be performed for the dichotomous respiratory complications and the use of corticosteroids. Linear regression analysis will be performed for the incidence of endotracheal intubations, and number of days on invasive ventilation, respiratory support, and supplemental oxygen. In both analyses will be corrected for GA and centre. A survival analysis will be performed for the time to intubation.	Hospital discharge
	**Gastro-intestinal:** - Solitary intestinal perforation - Necrotizing enterocolitis > stage 2 (Bell’s criteria) - Feeding problems (days with parental feeding after inclusion) - Body weight - Head circumference	Logistic regression analysis will be performed for SIP, NEC and feeding problems. Linear regression analysis will be performed for body weight and head circumference. Both analyses will be corrected for GA and centre.	Hospital discharge
	**Neurological:** - Intravenous haemorrhage - Clinical seizures - Periventricular leukomalacia	Logistic regression analysis will be performed for all neurological outcomes, corrected for GA and centre.	Hospital discharge
	**Complications:** - Incidence of late-onset sepsis - Meningitis after inclusion - Need for inotropes/ respiratory support	Logistic regression analysis will be performed for all complications, corrected for GA and centre.	Hospital discharge
	- Retinopathy of prematurity	Logistic regression analysis, corrected for GA and centre, will be performed for retinopathy ‘yes’ or ‘no’.	Hospital discharge
	- Hearing loss	Logistic regression analysis, corrected for GA and centre, will be performed for hearing loss ‘yes’ or ‘no’.	Hospital discharge
**Long-term outcomes**	- Readmission since first hospital discharge - Body weight - Body length - Head circumference - Behavioural problems (Child Behavior Checklist) - Cognitive and language development	Logistic regression analysis will be performed for readmissions, behavioural problems, and cognitive and language problems. Linear regression analysis will be performed for body weight, body length, and head circumference. In both analysis will be corrected for GA and centre. Survival analysis will be performed for the time to readmission.	Eighteen to 24 months of corrected age
**Cost-effectiveness**	- (Non-)medical costs during and after hospital admission - Patient outcomes; survival, severe disability, and health-related quality of life (HRQoL)	The total costs per patient and quality-adjusted life years (QALYs) will be assessed. Incremental cost-effectiveness ratios (ICERs) will be calculated, expressed as incremental costs per additional survivor without severe disability at 2 years and incremental costs per QALY gained.	Eighteen to 24 months of corrected age
**Pharmacokinetics**	- Blood samples	Exposure of (keto-) doxapram will be calculated from an existing PK model. The cumulative exposures will be calculated and analysed using a linear regression model, corrected for centre.	During level 3 NICU admission
**Respiratory effects**	- Vital sign data (oxygen saturation, respiratory rate, heart rate, blood pressure) - Ventilation data (ventilation mode, fraction of inspired oxygen, flow)	Vital sign data will be analysed as continuous data. Logistic regression analysis will be performed for all vital sign data, corrected for GA en centre. Mixed model analysis will be performed to take into account repeated measurements. Ventilation duration and cumulative inspired oxygen need and flow will compared using the *t*-test or Mann-Whitney test.	During level 3 NICU admission
**Cerebral effects**	- Cerebral oxygenation (rScO_2_; NIRS-derived) - Transfer function (rScO_2_ as surrogate for cerebral blood flow) - Neurological function (General movement assessment) - Cerebral activity (aEEG or full EEG)	Continuous outcome data will be compared using a two-sided stratified MWU (van Elteren test). For dichotomous data, a stratified *χ*^2^-test will be used. A linear mixed model for longitudinal measures using restricted cubic splines to model the relation between time and outcome will be used.	During level 3 NICU admission

Secondary, continuous outcomes will also be presented as mean and standard deviation if normally distributed, and as medians and interquartile range if not normally distributed. The Kolmogorov-Smirnov test will be performed to assess normality of continuous variables. Secondary, categorical outcomes will be presented as frequency and percentage. The outcomes will be compared between the doxapram and placebo group using the *t*-test or the Mann-Withney test in case of continuous data, and the chi-square test or Fisher’s exact test in case of categorical data

^a^The effect measures of logistic regression models will be presented as the odds ratios together with the 95% confidence intervals based on the profile likelihood. For linear regression models, robust standard errors computed with a sandwich estimator will be used for confidence intervals and significance tests. Effect measures of the Cox proportional hazards model will be presented as (conditional) hazard ratios together with 95% confidence intervals. Significance will be tested using the partial likelihood ratio test

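### Table 1 assigns logistic regression to vital signs declared continuous and to feeding days without a cut-off, and its linear models for respiratory day counts let early death count as few days

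*Protocol article*

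**What the plan says.** All three items stand in Table 1 of the protocol article.

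- **Vital signs (Respiratory effects row).** "Vital sign data will be analysed as continuous data". The next sentence reads "Logistic regression analysis will be performed for all vital sign data, corrected for GA en centre". A mixed model for repeated measurements follows, with no link function or outcome type given. The Secondary outcome analyses section sets the general rule: logistic regression for dichotomous secondary outcomes, linear for continuous ones.
- **Feeding (Gastro-intestinal row).** Feeding problems are defined by the number of days of parenteral feeding after inclusion (the table prints parental). The model is: "Logistic regression analysis will be performed for SIP, NEC and feeding problems". No number of days is named that would make the outcome yes or no.
- **Respiratory day counts (Respiration row).** "Linear regression analysis will be performed for the incidence of endotracheal intubations, and number of days on invasive ventilation"; the sentence goes on to include days on respiratory support and on oxygen. These models adjust for GA and centre, and the time of measurement is hospital discharge. The same row adds: "A survival analysis will be performed for the time to intubation". The table's footnote says that for linear models "robust standard errors computed with a sandwich estimator will be used for confidence intervals and significance tests", and the notes add a comparison by t-test or "Mann-Withney test in case of continuous data".

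Death appears elsewhere in the secondary analyses: on its own, combined with BPD, as time to death, and as a competing risk for severe disability. It does not enter the day-count models.

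**The concern.** For vital signs and feeding, the stated model does not match the stated outcome. Someone has to choose a cut-off or a different model later, and if that happens after data are seen it is a free choice.

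For the day counts, the model runs but may answer the wrong question. Days accrued to discharge stop at death, so an early death reads as a short respiratory course. Duration of mechanical ventilation is the first secondary outcome named in the abstract, and avoiding ventilation is the proposed route to benefit. If doxapram prevented deaths, it could look worse on these outcomes; if it caused deaths, it could look better. A mortality difference is something the plan itself allows for: the interim rule considers an absolute difference of at least 10% in either direction.

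**Working it through.** The article gives no figure for these outcomes, so there is none to reproduce.

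**1. Vital signs.** A standard logistic model needs an outcome coded 0/1, or at least lying between 0 and 1. Table 1 calls oxygen saturation, respiratory rate, heart rate and blood pressure continuous and gives no threshold. As a check, 396 simulated saturation values (assumed mean 92, SD 4) were given to a standard logistic fit; it stopped because the outcome must lie in the unit interval. The mixed-model sentence does not withdraw the logistic instruction.

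**2. Feeding.** The outcome is a number of days and the model is for a dichotomy. The two can be joined only by a cut-off, and none is stated. By the article's general rule, a day count treated as continuous would be analysed linearly.

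**3. Day counts, algebra.** Let m be mortality in an arm, S the mean days in survivors and D the mean days in infants who die. The arm mean is (1 − m)S + mD. If S and D are the same in both arms, the difference between arms is −(m₁ − m₀)(S − D). It is zero when mortality is equal and otherwise favours the arm with more deaths. S and D are assumed, because the documents give neither.

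| Assumed S and D | 3 points | 5 points | 10 points |
|---|---|---|---|
| Support days, 45 and 15 (S − D = 30) | 0.9 | 1.5 | 3.0 |
| Ventilation days, 12 and 5 (S − D = 7) | 0.21 | 0.35 | 0.70 |

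**4. Day counts, simulation.** There were 400,000 infants per arm and no true effect on days. Comparator mortality was 10% or 15%. For ventilation, about 45% had no ventilation days, the mean was about 8 days, sicker infants were more likely to die, and deaths fell on days 1–10. For support, the mean was about 50 days (SD 18), and deaths were at random on days 1–20. All of these are assumptions. Results are the treated arm minus the comparator, in days:

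| Mortality in treated arm | Ventilation days, all infants | Support days, all infants | Ventilation days, survivors only |
|---|---|---|---|
| Equal | −0.01 to 0.02 | 0.02 to 0.04 | −0.01 to 0.02 |
| 5 points lower | +0.58 to +0.75 | +2.00 to +2.05 | +0.56 to +0.69 |
| 10 points lower | +1.35 to +1.74 | +3.95 to +4.05 | +1.28 to +1.57 |

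The arm with fewer deaths looks worse. Restricting to survivors does not remove the ventilation artefact when sicker infants die. For support days, where deaths were simulated at random, it does (−0.02 to 0.08).

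**5. Whether the other planned analyses help.** Sandwich errors change the standard error, not the estimated difference. A Mann-Whitney test gives infants with few days the favourable ranks, whether or not they died. Time to intubation is a different outcome.

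**6. Whether linear regression itself fails.** With 198 per arm, no mortality difference and a robust-variance comparison of means without covariates (4,000 runs), type I error was 0.047 for skewed, zero-heavy days and 0.048 for a yes/no intubation outcome.

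**The case against.** The strongest reply on the day counts is that linear regression with robust errors is a legitimate method. It is computable, holds its error rate, and estimates the difference in mean days correctly. If the aim is resource use, days accrued by all infants are the right quantity. Death is also reported separately and jointly with BPD, so a careful reader can set ventilation days beside mortality. A rule for death may sit in the SAP, which is not shown, and the article's silence on that is not held against it. This reply stands to the extent that the problem is conditional: it needs a mortality difference, and every day figure above is assumed. It does not remove the problem, because the model the article names counts early death as a short course, and none of the other analyses it names changes that.

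On vital signs, the logistic sentence may be a slip for linear, a mixed model is planned as well, and high-frequency monitor data come from only some centres. That limits the consequence, but the sentences still contradict each other. On feeding, a cut-off may be given in the SAP; the article's definition as days still does not match its model.

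A reader might infer three stronger things that the documents do not support:

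- That these results will be biased. With equal mortality the artefact is about zero.
- That linear regression of intubation incidence is invalid. It holds its error rate for a yes/no outcome, and incidence may mean a count, so that choice is a matter of preference.
- That key secondary outcomes are at risk. The article labels no secondary outcome as key.

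**Conclusion.** The vital-sign entry is the firm part: it contradicts itself and the article's general rule, and cannot be run as written. The feeding entry is a mismatch of the same kind, resolved by a cut-off or another model. Neither conclusion rests on assumptions about the data.

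The day-count comparisons could be biased in favour of the arm with more deaths if mortality differs. Under the assumptions shown, a 5-point difference moves mean ventilation days by about 0.35 to 0.75 and support days by about 1.5 to 2.05; a 10-point difference moves them by about 0.7 to 1.74 and 3.0 to 4.05. These figures show scale only, since the real values depend on day counts and timing of death that the documents do not give. The primary composite counts death and is not touched.

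**What to change.** - **Vital signs.** Replace the logistic sentence with a linear mixed model adjusted for GA and centre, or define a binary outcome with its threshold. Bring Table 1 into line with the Secondary outcome analyses section.
- **Feeding.** Analyse the days with a count, linear or rank model, or state the cut-off that makes logistic regression apply.
- **Respiratory day counts.** Add an analysis that accounts for death: days alive and free of invasive ventilation, of respiratory support and of oxygen to a fixed time point, with death ranked worst. The 36-week postmenstrual age already used in Table 1 is one candidate time point. Use a stratified rank test (Table 1 already names the van Elteren test for the cerebral outcomes) or a proportional-odds model, and report the result beside mortality.

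The cost is mainly wording in Table 1 and the SAP. Day counts and time to death are already planned, but the case report form is not shown, so check that days can be counted to the chosen time point. The downside is interpretive: the effect becomes a composite of death and duration rather than a mean of raw days. Keep the raw-day means by arm as description.
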